#### Participant timeline {13}

After the consent process is completed, we will conduct baseline assessments. This will be followed by the 1:1 random allocation of the recruited participants to either MILAP or EUC. Participants will then receive the intervention based on their allocation. We will conduct follow-up assessments at 1, 3 6, 9, and 12 months from baseline for all participants, regardless of intervention allocation. To evaluate the effectiveness of individual MILAP components, the one-month follow-up assessment will take place immediately after the completion of all MIL-DIL sessions and prior to the start of the BCT sessions. The three-month follow-up will be conducted after participants have completed all nine MILAP sessions. Figure 2 below shows the study timeline.

#### Sample size {14}

Given the dual goals of the trial to assess MILAP’s effectiveness and understand mechanisms of action, sample size was determined for both mediation analyses and the impact on primary outcomes. Because mediation analysis is more statistically power-intensive, we calculated the sample size required to achieve 80% power to detect: a) the effect of the intervention on the primary outcome (the proportion of women with at least moderate depression), and b) a significant indirect effect of the intervention on depression, mediated by women’s FOM, one of the primary theorized mechanisms of change in our conceptual model. These calculations were based on the joint testing of both links in the hypothesized mechanistic pathway from intervention to FOM (link 1) and FOM to depression (link 2), using the approach of Vittinghoff and Neilands (78) and the corresponding medssp.R program. Based on our pilot study results, we expect the proportion of women with at least moderate depression (PHQ-9>9) post-intervention to be approximately 40% in the comparison group versus 5–10% in the intervention group. Based on the observed increase in FOM in the pilot study (65, 66), and to ensure clinical relevance, we specified a moderate effect of the intervention on the continuous FOM mediator, i.e., an R^2^ of 13% for FOM, per Cohen’s guidelines(79) for the first link, and an odds ratio of 0.5 per standard deviation (SD) of FOM for the dichotomous depression outcome for the second link of the indirect effect (i.e., a gain of 1 SD in FOM is associated with half the odds of scoring >9 on the PHQ-9). Assumptions for additional nuisance parameters that were necessary to be specified for this sample size calculation were: OR=0.77 for the direct effect of the intervention on depression (i.e., the remaining reduction in odds of PHQ-9 > 9 for the intervention group relative to EUC not mediated by FOM), and ρ_2_ = 0.30, a conventional moderate value (80) to account for correlation between the mediator and potential confounders. Given the 1:1 randomization, intervention exposure is 50% and it is reasonable to assume no confounding (ρ_1_ = 0) of the intervention-depression relationship. Based on these specifications, the required sample size was calculated to be n=251. To account for an anticipated attrition rate of approximately 15%, we determined an initial sample size of n=300 triads.

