MILAP is informed by Social Cognitive Theory (SCT) (54–57) and findings from our pilot studies (Figure 1). SCT offers a culturally appropriate model that emphasizes interpersonal dynamics, the role of family environments in shaping behavior, and strategies to reduce barriers while enhancing facilitators of healthy behavior change.(55, 58) As women in the study setting have fewer options to leave their marriage (19), are heavily affected by the views and behaviors of their family members (37), and are committed to staying married, SCT allows us to incorporate these factors at the women’s individual, interpersonal and family levels. Given that IPV contributes to depression through mechanisms such as social isolation, restricted mobility, diminished self-efficacy and negative family dynamics, MILAP specifically targets determinants identified as modifiable in our prior research.(6–12, 59). Evidence supports the integration of IPV and mental health interventions that build problem-solving skills (60), strengthen relationships with key family members (61, 62), promote social support (63), and enhance resilience and empowerment.(64) MILAP addresses IPV and depression in a non-stigmatizing and depersonalized manner, and offers coping skills for women, mutual empowerment of MILs and daughters-in-law (DILs), and enhanced spousal communication and trust.

We conducted two single-arm pilot studies to test the acceptability, feasibility, and preliminary impact of MILAP, and found it to be well-accepted and effective in addressing IPV, depression and PTSD among young married women.(65, 66) In this manuscript, we report the protocol for a community-based fully-powered two-arm randomized controlled trial involving 300 families to evaluate the effectiveness of MILAP in reducing IPV, and improving depression and PTSD symptoms among **young married women aged 15–24**. Moreover, this randomized controlled trial will include cost-effectiveness analyses to evaluate the health and economic benefits of investing in MILAP, thereby assisting policymakers and payors in assessing MILAP’s potential for future scalability.

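### The sample-size inputs contradict each other: the mediation assumptions imply about 24–25% depression under MILAP, not 5–10%, and on those inputs the total depression effect, not mediation, is the demanding target

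*Protocol article*

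**What the plan says.** All the inputs stand in the Protocol article, Sample size {14}. The section says "we calculated the sample size required to achieve 80% power to detect" two targets. Target (a) is MILAP's effect on the share of women whose PHQ-9 score is above 9. Target (b), the mediation target, is described as "a significant indirect effect of the intervention on depression, mediated by women’s FOM". The section presents mediation as the harder of the two to power and says the calculation rests on testing both links of the pathway jointly.

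It gives two descriptions of the effect on depression:

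- From the pilot work, the proportion with PHQ-9 above 9 is expected "to be approximately 40% in the comparison group versus 5–10% in the intervention group".
- For the calculation, it takes "an R^2^ of 13% for FOM" as the effect of the intervention on the mediator, an odds ratio of 0.5 per SD of FOM for depression, and "OR=0.77 for the direct effect of the intervention on depression". The last is explained as the part of the effect that does not pass through FOM. The correlation of the mediator with confounders is 0.30 and allocation is 1:1.

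From these, "the required sample size was calculated to be n=251", raised to 300 triads for about 15% attrition.

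**The concern.** The direct odds ratio is defined as everything not carried by FOM, so the indirect and direct parts together make up the whole effect on depression. No further pathway can close a gap between that total and the expected rates. The two descriptions should therefore give about the same MILAP rate, and they do not.

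Depression is one of the two primary outcomes. If the halves of the section disagree, a reader cannot tell whether the trial is sized for a difference of 30–35 percentage points or of about 15–16. That matters when a modest or null result has to be interpreted. If the target named as the driver is not the one that produces 251, the stated justification for the sample size is also misleading.

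**Working it through.** Inputs are those listed above. The section gives no significance level; two-sided 0.05 is assumed, so (1.960 + 0.842)² = 7.849 at 80% power.

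**Attrition.** 251/0.85 = 295.3, rounded to 300; 300 × 0.85 = 255, which is at least 251. This step is sound.

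**Total effect implied by the mediation inputs**

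- Shift in FOM at 1:1 allocation: √0.13/0.5 = 0.721 SD.
- Indirect log odds ratio: 0.721 × ln 0.5 = −0.500, odds ratio 0.607.
- Direct log odds ratio: ln 0.77 = −0.261.
- Sum: −0.761, total odds ratio 0.467.
- MILAP odds: (0.40/0.60) × 0.467 = 0.311, so the rate is 0.311/1.311 = 23.7%.
- Averaging the logistic curve over FOM (residual variance 0.87, comparison group held at 40%) gives 24.8%.

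**What 5–10% would need**

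- Total odds ratio: (0.05/0.95)/(0.40/0.60) = 0.079 and (0.10/0.90)/(0.40/0.60) = 0.167.
- Direct odds ratio: 0.079/0.607 = 0.13 and 0.167/0.607 = 0.27. With averaging over FOM it is 0.11 and 0.24. The stated value is 0.77.

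**Reproducing 251 through target (a)**, 40% versus 23.7%

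- Unpooled difference in proportions: 2 × 7.849 × (0.240 + 0.181)/0.1625² = 250.2, rounded up to 251.
- Pooled formula: 255.7, rounded up to 256.
- Logistic Wald test at mean prevalence 0.319: 7.849/(0.761² × 0.25 × 0.319 × 0.681), about 250.

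**Size for target (b)**, joint test

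- Link 1: 7.849 × 0.87/0.13 = 52.5.
- Link 2: 7.849/[(ln 0.5)² × V × (1 − 0.30²) × p(1 − p)], with V the FOM variance (1 or 0.87) and p the overall depression prevalence. This gives 74.8 at p = 0.40, V = 1, and 118.3 at p = 0.225 (the mean of 40% and 5%), V = 0.87.
- Requiring both links at once gives 85 to 121. Simulation with a confounder correlation of 0.3 gives joint power of about 0.79–0.82 at n = 120 and 0.99 at n = 251. A harsher variance deduction in link 2 raises the formula's upper end to about 139, still far below 251.

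**Power at 251 analysed (125.5 per arm)**

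| Target and MILAP rate | Power |
|---|---|
| (a) 23.7% | 80.1% unpooled, 79.3% pooled |
| (a) 24.8% | about 73% |
| (a) 5–10% | above 99.9% (80% needs only 44–64 women in total) |
| (b) stated inputs | about 98–99% |

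**The case against.** The strongest reply is that 251 is sound and that sizing on a weaker effect than the pilots suggest is cautious. The section says a moderate FOM effect was chosen for clinical relevance. Much of this stands: 251 is reproduced from the mediation inputs, and enrolment need not change. It does not remove the contradiction, because the section never says that the expected rates and the design effect differ.

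The ranking of the two targets can also be defended if 40% versus 5–10% is the design effect. Target (a) then needs only 44–64 women and mediation is indeed the harder target. But the specified direct odds ratio does not produce those rates, and neither requirement is then close to 251.

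Four stronger readings are tempting and not supported:

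- *That 251 follows from nothing stated.* It matches target (a) at 23.7% by standard formulas.
- *That 80% power is wrong for both targets.* Target (a) has about 79–80% by the simple odds product, and target (b) exceeds 80%, which is no error. The drop to about 73% needs averaging over FOM, a refinement the section does not adopt.
- *That 251 came from applying the MILAP rate to everyone.* The link-2 formula does give about 251 at a prevalence near 8–9%, but the section does not say that this was done, and the program it names is not available to check.
- *That 40% is presented as an observed control rate.* The Background section says "We conducted two single-arm pilot studies to test the acceptability, feasibility, and preliminary impact of MILAP", so no comparison group was observed. But the sample-size text words 40% as an expectation, so this is not a misstatement.

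**Conclusion.** The contradiction holds. The mediation inputs imply about 24–25% depression under MILAP (total odds ratio 0.47), and 5–10% (total odds ratio 0.08–0.17) cannot describe the same trial. The stated basis for 251 is also wrong on those inputs: the joint test needs about 85–125 women, and the total effect on depression about 250–256 (about 297 at 24.8%).

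This rests on two-sided 0.05, which the section does not state. That 251 was derived from target (a) is an inference from matching figures, because the program used is not available. The comparison of rates depends on neither; it follows from the stated inputs alone. The consequence is for interpretation and reporting, not for enrolment.

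**What to change.** Keep 300 triads and rewrite the section around one coherent set of inputs, with the depression rate by arm and the significance level used. There are two ways to do it:

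- Keep the direct odds ratio of 0.77 and give the MILAP rate used for design as about 24–25%, with 5–10% labelled as the more optimistic expectation from the pilots. State, once the sponsor has confirmed it against the original calculation, that the total depression effect determines 251, and correct the sentence that calls mediation the harder target.
- Keep 40% versus 5–10% as the design effect and change the direct odds ratio to about 0.11–0.27. In that case 251 exceeds what either target needs, and the section must say why it was chosen.

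Under the first option, restate power at 251 analysed as about 79–80% for the depression effect at 23.7% (about 73% at 24.8%) and about 98–99% for the indirect effect. Under the second, power for depression is above 99.9%, and mediation power should be recalculated with the new direct odds ratio.

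The cost is a text correction. Under the first option the stated design effect becomes less favourable than the one now printed.

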#### Recruitment {15}

To enroll a total of 300 families, we anticipate that research assistants will have to screen about 800 families. To facilitate recruitment, we will share study information with the Female Community Health Volunteers (trained local health volunteers who provide community-based education and services focused on maternal and child health, and family planning) (81, 82), groups from WOREC networks like mothers’ groups and adolescent groups, and local stakeholders like local municipal authorities. Additionally, we will establish a community advisory board comprising independent community representatives (e.g. local leaders, women human rights defenders, and representatives from local community-based organizations actively engaged in IPV and mental health-related work). The board will provide independent feedback and guidance to strengthen the study process, including recruitment strategies, and to help safeguard the safety of study participants.

After receiving a referral of potential woman participant, a research assistant will contact her and schedule an in-person appointment to assess eligibility. Given the stigma surrounding IPV and mental health, the research assistant will initially present the study as a family well-being intervention focused on reducing family conflict, and strengthening caring and supportive relationships. If the woman is eligible and provides permission to contact her family, the research assistant will then meet with her husband and mother-in-law (MIL) to confirm their eligibility. The recruitment flow is illustrated in Figure 3

### Assignment of interventions: allocation

#### Sequence generation {16a}

The data manager, who doesn’t have any direct interaction with participants and is not involved in data collection, will randomly assign each family triad to MILAP or EUC using a random number generator. We will conduct 1:1 randomization stratified by district.

#### Concealment mechanism {16b}

We will reveal intervention allocation to participants, research assistants, and counselors after randomization. We will, however, conceal the intervention allocation from assessment staff who conduct baseline and follow-up assessments. Assessment staff will be solely responsible for conducting baseline and follow-up assessments. They will not participate in any trainings, discussions, or activities that involve sharing information about the intervention. Research assistants will request the assessment staff to conduct the baseline and follow-up assessments as per the study timeline.

#### Implementation {16c}

Once the random allocation is generated, the data manager will reveal it first to the research coordinator who will then inform the research assistant using secured and confidential communication channel. The research assistant will then reveal the intervention allocation directly to participants via phone or in-person.

### Assignment of interventions: Blinding

#### Who will be blinded {17a}

The study team member who will conduct assessment, i.e. assessment staff, will be blinded. Since MILAP is a behavioral intervention that is unique (involving woman, husband, and MIL), participants receiving the intervention cannot be blinded. In addition, research assistants will not be blinded, as they are for responsible for coordinating with participants and counselors to schedule MILAP sessions.

#### Procedure for unblinding if needed {17b}

We do not anticipate needing to unblind.

### Data collection and management

#### Plans for assessment and collection of outcomes {18a}

We will use the REDCap platform to collect quantitative data. We will administer all assessment tools to both MILAP and EUC participants. We will administer demographic tool and prior adverse childhood experiences tool at baseline only. All other assessment tools will be administered at baseline and at follow-up time points: 1, 3, 6, 9, and 12 months post-baseline.

Depression will be measured using the widely used PHQ-9 tool, which is well-validated in Nepal.(70) We will use the IFVCS to measure abusive control, physical violence and sexual violence (77), and the PCL-C to measure PTSD.(83) Details of all outcomes measures, including demographic variables, are presented in Table 2.

To assess the mechanisms of change underlying MILAP’s effectiveness, we will collect qualitative data through serial in-depth interviews (IDIs) with all three members of the triad. We plan to conduct serial IDIs with approximately 15% of MILAP participants (n = 66), based on resource availability and the estimated number needed to reach thematic saturation (22 triads). We will conduct these serial IDIs at two timepoints: after the completion of MILAP and at the 12-month follow-up. We will purposively select triads to reflect variation in engagement with MILAP (e.g., across geographic areas and counselors), allowing us to capture a diverse range of intervention experiences. We will interview each participant separately using a semi-structured guide.

To conduct the cost-effectiveness analysis, we will collect data on the average costs per triad for delivering MILAP and EUC. We will also collect costs associated with each component of MILAP i.e. MIL-DIL, BCT, and the triad component. We will assess costs from a health system perspective, capturing both direct costs (e.g., staff time, training, materials, logistics) and indirect costs (e.g., monitoring, supervision, overhead, and administrative expenses) associated with implementation. In addition, we will capture costs incurred by participants and their households, including: (a) out-of-pocket expenses related to participation in the intervention (e.g., transportation and incidental costs), and (b) time costs, such as lost wages or productivity, due to time spent accessing and participating in the intervention.

#### Plans to promote participant retention and complete follow-up {18b}

We will utilize the strategies we have for intervention adherence (see above) for completing follow-up assessments. We will conduct assessments at a time and place that is convenient and preferred by participants. We will offer breaks as needed during assessments and provide a small financial incentive in appreciation of participants’ time.

#### Data management {19}

We will use the REDCap mobile app, which allows offline data collection using tablets. Trained research staff will collect and enter data on password-protected, encrypted tablets, and transfer it securely to the REDCap system, also password-protected, within 24 hours of data collection. We will conduct weekly data quality check to assess accuracy and completeness. Additionally, we will conduct monthly quality control checks to ensure data integrity and protocol adherence, identify any potential data issues early, and resolve them promptly. We will use STATA to process and manage quantitative data, and Dedoose for qualitative data management.

#### Confidentiality {27}

To ensure confidentiality in data collection and management, we will use the HIPAA-compliant REDCap mobile application on password-protected tablets for secure collection of responses. We have trained research assistants, assessment staff and counselors on maintaining participant confidentiality. We will assign different level of responsibility and REDCap login to safeguard data security, privacy and confidentiality. Login access will be managed through a two-factor authentication system and each user will be granted role-specific access (entry, view, or edit) based on their responsibilities within the study. To minimize potential contamination, we will implement several strategies: assign separate counselors to conduct MILAP and EUC sessions; restrict MILAP training to counselors delivering the intervention; and train both counselors and staff in controlled communication and contamination-mitigation techniques.Additionally, we have developed a research ethics brief to guide all study team members in the ethical conduct of the research involving vulnerable populations.(84)

#### Plans for collection, laboratory evaluation and storage of biological specimens for genetic or molecular analysis in this trial/future use {33}

Not applicable. We will not collect any biological specimens for genetic or molecular analysis in this trial/future use.

### Statistical methods

#### Statistical methods for primary and secondary outcomes {20a}

To evaluate the effectiveness of MILAP in reducing the proportion of women with moderate to severe depression and the levels of IPV and PTSD, we will conduct intention-to-treat (ITT) regression analyses at the end of the trial (12-month follow-up, single timepoint). Additionally, we will perform longitudinal analyses using a two-level regression model, incorporating an interaction between intervention arm and time, with repeated measures nested within participants (i.e., women) and a random intercept for participants. We will use logistic regression models for the binary outcomes (like depression defined by PHQ-9>9), and linear models for the continuous outcomes (like IFVCS score for IPV and PCL-C score for PTSD).

We will use thematic analysis to examine qualitative data from serial in-depth interviews (n = 66 across 22 triads). These interviews will help identify and prioritize potential mediators and moderators for quantitative analysis. We will triangulate the qualitative findings with quantitative data from the full cohort (n = 900 across 300 triads) and conduct a mixed-methods explanatory analysis to develop a comprehensive understanding of the mechanisms through which MILAP produces the intended outcomes and the relative contribution of each mechanism. To explore the mechanisms of change outlined in the conceptual model, we will conduct mediation analyses to assess whether, for example, the DIL-reported freedom of movement (FOM) score mediates the relation between intervention exposure and odds of DIL’s PHQ-9 >9. This will be examined by a structural equation model which simultaneously models the effect of the intervention on FOM (a), and of FOM (b) and intervention (c’) on depression, with a significant indirect effect (a*b) indicating mediation. (85) The model allows for continuous as well as categorical mediators and outcomes, and for multiple mediators to be included in the same model, to compare their relative impact.(86) We will use similar approach for other primary and secondary outcomes.

For cost-effectiveness analyses, we will conduct a trial-based cost-effectiveness analysis of MILAP at the 12-month follow-up, focusing on two primary outcomes: (1) cost per case of moderate to severe depression averted (PHQ-9 >9), and (2) cost per IPV event averted. Costs will be estimated from both health system and societal perspectives. We will use a bottom-up micro-costing approach at the family triad level to estimate intervention costs. At the facility level, we will apply time-driven activity-based costing, a participant-centered method that measures detailed resource use across service delivery processes.(87) We will also calculate incremental cost-effectiveness ratios by comparing differences in costs and outcomes between the MILAP and EUC groups.

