#### Outcomes {12}

This study has two primary outcomes. The first primary outcome is the change in the proportion of women with moderate to severe depression from baseline to the 12-month follow-up. To assess depression severity, we will use the PHQ-9, which has been validated in Nepal, and define moderate to severe depression as a PHQ-9 score of greater than nine.(70) The second primary outcome of interest is the change in IPV levels from baseline to the 12-month follow-up. We will assess IPV through measures of abusive control, physical violence, and sexual violence using the Indian Family Violence and Control Scale (IFVCS).(77) Our secondary outcome of interest is the severity of PTSD symptoms, measured by the PTSD CheckList-Civilian Version (PCL-C). Detailed information on primary, secondary and other outcome measures is presented in Table 2.

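### Both primary outcomes are defined as change from baseline, but the 12-month models name neither the baseline value nor district; the loss is precision, mainly for IFVCS and PCL-C, and a clear estimand

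*Protocol article*

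**What the plan says.** Outcomes {12} of the protocol article defines both primary outcomes as change. For depression: "The first primary outcome is the change in the proportion of women with moderate to severe depression from baseline to the 12-month follow-up". For violence: "The second primary outcome of interest is the change in IPV levels from baseline to the 12-month follow-up".

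Statistical methods for primary and secondary outcomes {20a} evaluates effectiveness by "intention-to-treat (ITT) regression analyses at the end of the trial (12-month follow-up, single timepoint", with logistic models for binary outcomes and "linear models for the continuous outcomes (like IFVCS score for IPV and PCL-C score for PTSD". It then adds a second analysis: "Additionally, we will perform longitudinal analyses using a two-level regression model, incorporating an interaction between intervention arm and time", with a random intercept for each woman. The only model terms listed (arm, time, their interaction, the woman's intercept) belong to this additional model. No terms are listed for the 12-month models.

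Sequence generation {16a} says: "We will conduct 1:1 randomization stratified by district". District is not mentioned again in the analysis text. The baseline scores will exist, because Plans for assessment {18a} says: "All other assessment tools will be administered at baseline and at follow-up time points: 1, 3, 6, 9, and 12 months post-baseline". Participant timeline {13} places the baseline assessment before allocation.

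Sample size {14} covers depression and its mediation by freedom of movement. It shows no calculation for the IFVCS.

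**The concern.** The outcome definition and the stated model do not describe the same analysis. A reader could analyse the 12-month value alone, a change score, or the 12-month value adjusted for baseline. For a continuous score all three target the same expected arm difference, but their precision differs. That matters most for the IFVCS, a primary outcome for which the article shows no power calculation.

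For PHQ-9 > 9, a change in a proportion is an absolute quantity, while a logistic model yields an odds ratio. The effect measure that answers the stated outcome is therefore not named. The randomisation is also stratified by district, and a model that leaves district out does not use that feature of the design.

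**Working it through.** **1. The plan's own figures.** 251/0.85 = 295.3, so 296, which is consistent with enrolling 300. The 251 itself cannot be reproduced exactly, because the article does not give the significance level or the overall outcome prevalence used. I take it as the number analysed and assume two-sided alpha 0.05. At the stated 40% against 5–10%, 22–32 women per arm give 80% power, and power at 125 per arm exceeds 99.9%.

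**2. Is the 12-month contrast biased?** The expected arm difference in change is (12-month difference) minus (baseline difference). Randomisation makes the expected baseline difference zero. The two contrasts therefore agree in expectation, on the mean scale and on the proportion scale.

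**3. Linear models (IFVCS, PCL-C).** Let r be the correlation between baseline and 12 months. The article does not give it; r = 0.3–0.6 is assumed. Relative to the 12-month value alone, the variance of the arm difference is 1 − r² with baseline adjustment and 2(1 − r) for a change score. Without adjustment, the difference detectable with 80% power at N = 251 is (1.960 + 0.842) × 2/√251 = 0.354 SD. Adjusted power at that difference is Φ(2.802/√(1 − r²) − 1.960).

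| r | Variance, 1 − r² | Equivalent extra women, 1/(1 − r²) − 1 | Detectable difference | Adjusted power at 0.354 SD | Change-score power at 0.354 SD |
|---|---|---|---|---|---|
| 0.3 | 0.91 | 10% | 0.337 SD | 84% | 66% |
| 0.5 | 0.75 | 33% | 0.306 SD | 90% | 80% |
| 0.6 | 0.64 | 56% | 0.283 SD | 94% | 88% |

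The 12-month value alone has 80% power in every row. Baseline adjustment against a change score gives a variance ratio of (1 − r²)/(2(1 − r)) = (1 + r)/2 = 0.65, 0.75 and 0.80. Adjustment is the most precise of the three readings throughout this range. A change score is worse than the 12-month value alone when r is below 0.5.

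**4. PHQ-9 > 9.** Logistic regression was simulated with and without a baseline score and two district indicators (N = 252, three equal districts, 1,500 replicates per scenario, latent correlation 0.3–0.5, district shifts of 0.2–0.4 latent SD; all of these settings are assumed).

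- At 40% against 10%, power is above 99% with or without adjustment.
- At 40% against 25%, power rises from about 72% to 76–82%. The standard error of the log odds ratio also rises, from 0.276 to 0.290–0.322, while the log odds ratio moves from about −0.70 to between −0.76 and −0.92. The adjusted odds ratio is a different, conditional quantity.

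The 25% is relevant because the path values in Sample size {14} lead to it. R² = 0.13 is a shift of 2√0.13 = 0.72 SD in freedom of movement. With an odds ratio of 0.5 per SD, a direct odds ratio of 0.77 and 40% in the comparison arm, the implied proportion under MILAP is 24.8%.

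**5. District.** With no true effect (40% in both arms), simulated type I error was 3.1–4.9% without adjustment and 4.5–5.7% with it. The simulation error near 5% is √(0.05 × 0.95/1500) = 0.6 percentage points. Only the 3.1%, seen under the strongest assumed district effect, stands clearly away from 5%, and it lies on the conservative side.

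**The case against.** The strongest reply is that the article never calls its 12-month models unadjusted. A reader might infer that from the terms it lists, but those terms describe the additional longitudinal model. Covariate lists are commonly left to a full protocol or analysis plan, and neither is shown here. This stands: the documents do not support saying that the sponsor has chosen an unadjusted analysis. What remains is a mismatch within the text itself, since the outcomes are defined as change and the main analysis is fixed at one timepoint.

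The arm-by-time model does address change if baseline is one of its repeated measures. The article does not say whether it is, and it presents that model as an addition.

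A reader might also infer a validity problem from ignoring the strata. The check shows at worst a conservative test, so that inference fails.

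Nor should one conclude that the cost-effectiveness analysis will rest on an odds ratio. Its outcome is "cost per case of moderate to severe depression averted (PHQ-9 >9", and the same section plans to compare differences in costs and outcomes between the arms, which is already a difference scale.

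Finally, the size of the gain rests on assumed correlations. Eligibility requires IPV in the past 12 months and excludes violence leading to hospitalisation. That may narrow the IFVCS range and lower r.

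**Conclusion.** The point holds as a matter of precision and estimand, not of bias or false positives. The definitions in Outcomes {12} and the model in Statistical methods {20a} need to be reconciled, and the better reconciliation is available at no cost in data.

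For the IFVCS and PCL-C the variance of the arm difference falls by 9–36% for r = 0.3–0.6, equivalent to 10–56% more women. This is an assumed range, and the gain requires only that r is not zero.

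For PHQ-9 > 9 it would be wrong to promise a gain in general. Adjustment widens the standard error of the log odds ratio, changes the odds ratio to a conditional one, and alters nothing material at 40% against 5–10%. It helps power only if the effect is smaller than planned, by about 4 to 10 percentage points at 40% against 25% under the assumed correlations.

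**What to change.** In Statistical methods {20a}, state the 12-month models in full:

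- IFVCS and PCL-C: linear regression on arm, baseline score and district.
- PHQ-9 > 9: logistic regression on arm, continuous baseline PHQ-9 and district, reported as a standardised (marginal) risk difference with confidence interval alongside the odds ratio, because adjustment makes the odds ratio conditional.

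In Outcomes {12}, reword both primary outcomes to match, as the difference between arms at 12 months adjusted for baseline.

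The cost is wording plus three degrees of freedom per model (one for baseline, two for the three districts). Nothing new has to be collected. If an unseen analysis plan already specifies these terms, only the article's wording needs to be brought into line. The change should be made before outcome data by arm are examined.
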